**FOR MALES ONLY**

A9. Altogether, how many wives do you have or other partners do you live with as if married?

__________ Total number of wives and live-in partners  *Skip to A11*

*_____ -1. Don’t know*

*_____ -2. Refused*

**FOR FEMALES ONLY**

A10. Including yourself, in total, how many wives or other partners does your husband/partner live with now as if married?

__________ Number of wives and live-in partners

*_____ -1. Don’t know*

*_____ -2. Refused*

**FOR BOTH MALES AND FEMALES**

A11. How long have you been living with your husband/wife/partner?

_____1. Number of days

**_____**2. Number of weeks

_____3. Number of months

_____4. Number of years

*_____ -1. Don’t know month*

*_____ -1. Don’t know year*

*_____ -2. Refused*

A12. Do you have any children?

_____ 0. No  *Skip to A16*

_____ 1. Yes

*_____ -1. Don’t know*

*_____ -2. Refused*

A13. How many children do you have that are living?

__________ Number of children

*_____ -1. Don’t know*

*_____ -2. Refused*

A14. How many of your children are living with you now?

__________ Number of children  *If 0, skip to A16*

*_____ -1. Don’t know*

*_____ -2. Refused*

A15. What is the age of your youngest child living with you now?

__________ Age of youngest child

A16. Have you done any paid work in the last 6 months?

_____ 0. No  *Skip to A18*

_____ 1. Yes

*_____ -1. Don’t know*

*_____ -2. Refused*

A17. Have you done any paid work in the last 7 days?

_____ 0. No

_____ 1. Yes  *Skip to A19*

*_____ -1. Don’t know*

*_____ -2. Refused*

A18. What is the main reason you are not working for pay now? *[Tick all that apply. Prompt with answer choices if needed.]*

_____ 1. Work occasionally

_____ 2. Work certain times of year

_____ 3. Study/in school

_____ 4. Am married

_____ 5. Spouse against me working

_____ 6. Taking care of children

_____ 7. Need to help in the house

_____ 8. No need to/don’t like

_____ 9. Health problems

_____ 10. Was fired

_____ 11. Can’t find work

_____ 12. Husband/wife/partner supports me

_____ 13. Other (specify) _______________

*_____ -1. Don’t know*

*_____ -2. Refused*

A19. What is your monthly household income? By household, I mean you and your spouse or partner who lives with you.

__________1. Kenyan Shillings

__________2.Namibian Dollars

__________3. Tanzanian Shillings

__________4. Other

If other, please specify which: _______________________

*_____ -1. Don’t know*

*_____ -2. Refused*

| ***Interviewer reads:*** *“*The next questions are about the household where you live/stay. Exclude corridors, walkways, and storage areas.” |
| --- |

A20. How many separate rooms are in your house, including all living areas, bathrooms, washrooms, and any other rooms? Please do not include outside bathrooms.

__________ Number of rooms

*_____ -1. Don’t know*

*_____ -2. Refused*

A21. How many rooms in this household are used for sleeping?

__________ Number of sleeping rooms

*_____ -1. Don’t know*

*_____ -2. Refused*

A22. How many people usually live in your household, including yourself and other adults or children?

__________ Number of people in household

*_____ -1. Don’t know*

*_____ -2. Refused*

| ***Interviewer reads:*** *“*The next questions are about travel to get to this clinic.” |
| --- |

A23. How far in kilometers is your house from this clinic?

__________ Distance in kilometers [1 km = 0.62 miles]

__________ Distance in miles

*_____ -1. Don’t know*

*_____ -2. Refused*

A24. How long does it usually take you to get from your house to this clinic?

__________ Time in minutes [1 hour = 60 minutes]

__________ Time in hours

*_____ -1. Don’t know*

*_____ -2. Refused*

A25. What is your primary means of transportation to this clinic? *[Tick all that apply.]*

_____ 1. Walking

_____ 2. Bicycle

_____ 3. Matatu or dala dala or bus/taxi

_____ 4. Motorcycle

_____ 5. Privately owned car

_____ 6. Special hire taxi

_____ 7. Boat/ferry

_____ 8. Other (specify) ____________________

*_____ -1. Don’t know*

*_____ -2. Refused*

A26. How much money does it cost for you to travel from your house to this clinic one-way?

_____1. Kenyan Shillings

_____2.Namibian Dollars

_____3. Tanzanian Shillings

_____4. Other

If other, please specify which: ______________________

*_____ -1. Don’t know*

*_____ -2. Refused*

A27. Have there been times you were scheduled to come to the clinic or needed to come to the clinic but you were not able to come?

_____ 0. No  *Skip to B1 in next section*

_____ 1. Yes

*_____ -1. Don’t know*

*_____ -2. Refused*

A28.Why were you not able to make it to the clinic*? [Read all options. Tick all that apply.]*

_____ 1. Not able to get away from work

_____ 2. Not able to pay for transportation

_____ 3. No transportation to clinic

_____ 4. Don’t want people to know I am coming to the clinic

_____ 5. Don’t have enough time to come to clinic

_____ 6. Other: Specify _______________________________

_____ 7. Other: Specify _______________________________

*_____ -1. Don’t know*

*_____ -2. Refused*

**HIV Testing and Care**

| ***Interviewer reads:*** *“*Now I am going to ask you some questions about HIV testing and your HIV care.” |
| --- |

B1. When did you find out that you have HIV?

|  |  |
| --- | --- |

[ mm / yyyy ]

*_____ -1. Don’t know*

*_____ -2. Refused*

B2. Where were you tested for HIV?

**_____** 1.VCT (Voluntary Counseling and Testing) centre

**_____** 2. PMTCT clinic

**_____** 3. Community testing

**_____** 4. Inpatient

**_____** 5. Outpatient

**_____** 6. Other (specify) _____________________________

*_____ -1. Don’t know*

*_____ -2. Refused*

B3. Why were you tested for HIV? *[Read all options. Tick all that apply.]*

_____ 1. Doctor encouraged me to get tested

_____ 2. Family or friend encouraged me to get tested

_____ 3. My partner was tested

_____ 4. I heard on the radio/TV that I should get tested

_____ 5. I was pregnant and the clinic tested me

_____ 6. I felt sick

_____ 7. Other (specify) ________________

*_____ -1. Don’t know*

*_____ -2. Refused*

B4. When was the last time your CD4 count was tested?

|  |  |
| --- | --- |

[ mm / yyyy ]

*_____ -1. Don’t know*

*_____ -2. Refused*

B5. What was your CD4 count last time you were tested?

_____ [CD4 count]

*_____ -1. Don’t know*

*_____ -2. Refused*

B6. How long after you learned you were HIV positive did you go to an HIV clinic for care? *[If started getting care immediately, write ‘0’ in for the month.]*

_________ Months

_________ Years

*_____ -1. Don’t know*

*_____ -2. Refused*

B7. How many total times in the past 6 months have you been to this clinic?

__________ Number of times

*_____ -1. Don’t know*

*_____ -2. Refused*

B7a. How many of these times did you just pick up HIV medications and not see a health care provider?

__________ Number of times

***_____*** *-1. Don’t know*

*_____ -2. Refused*

B8. Were you getting HIV care, treatment, or HIV medications at other clinics before coming to this clinic?

_____ 0. No

_____ 1. Yes

***_____*** *-1. Don’t know*

*_____ -2. Refused*

**Physical and Mental Functioning**

| ***Interviewer Reads:*** *“*Now I am going to ask you some questions related to your health.” |
| --- |

C1. Overall, how would you rate your health during the past 4 weeks?

_____ 1. Excellent

_____ 2. Very Good

_____ 3. Good

_____ 4. Fair

_____ 5. Poor

_____ 6. Very Poor

*_____ -1. Don’t know*

*_____ -2. Refused*

C2. During the past 4 weeks, how much did physical health problems limit your usual physical activities (such as walking or climbing stairs)?

_____ 1. Not at all

_____ 2. Very little

_____ 3. Somewhat

_____ 4. Quite a lot

_____ 5. Could not do physical activities

*_____ -1. Don’t know*

*_____ -2. Refused*

C3. During the past 4 weeks, how much difficulty did you have doing your daily work, both at home and away from home because of your physical health?

_____ 1. Not at all

_____ 2. A little bit

_____ 3. Some

_____ 4. Quite a lot

_____ 5. Could not do daily work

*_____ -1. Don’t know*

*_____ -2. Refused*

C4.How much bodily pain have you had during the past 4 weeks?

_____ 1. None

_____ 2. Very mild

_____ 3. Mild

_____ 4. Moderate

_____ 5. Severe

_____ 6. Very Severe

*_____ -1. Don’t know*

*_____ -2. Refused*

C5. During the past 4 weeks, how much energy did you have?

_____ 1. Very much

_____ 2. Quite a lot

_____ 3. Some

_____ 4. A little

_____ 5. None

*_____ -1. Don’t know*

*_____ -2. Refused*

C6. During the past 4 weeks, how much did your physical health or emotional problems limit your usual social activities with family or friends?

_____ 1. Not at all

_____ 2. Very little

_____ 3. Somewhat

_____ 4. Quite a lot

_____ 5. Could not do social activities

*_____ -1. Don’t know*

*_____ -2. Refused*

C7. During the past 4 weeks, how much have you been bothered by emotional problems (such as feeling anxious, depressed, or irritable)?

_____ 1. Not at all

_____ 2. Slightly

_____ 3. Moderately

_____ 4. Quite a lot

_____ 5. Extremely

*_____ -1. Don’t know*

*_____ -2. Refused*

C8. During the past 4 weeks, how much did personal or emotional problems keep you from doing your usual work, school, or other daily activities?

_____ 1. Not at all

_____ 2. Very little

_____ 3. Somewhat

_____ 4. Quite a lot

_____ 5. Could not do daily activities

*_____ -1. Don’t know*

*_____ -2. Refused*

**Perceived Availability of Support**

| ***Interviewer reads:*** “The following questions have to do with the support you get from people in your life. I will read you a series of questions concerning different types of help people might give you. Please tell me whether someone would be available to provide that kind of help or support if you needed it. Remember that I’m not asking whether or not you need this kind of help at this time, but whether someone could help you if you needed. Please answer ‘yes’ or ‘no’ to each of these questions.” |
| --- |

*[****Interviewer:*** *Circle the correct answer for each question.]*

|  | **No** | **Yes** | *Not Applicable* |
| --- | --- | --- | --- |
| D1. Would someone be available to talk to you if you were upset, nervous or depressed? | 0 | 1 |  |
| D2. Is there someone you could contact if you wanted to talk about an important personal problem you were having? | 0 | 1 |  |
| D3. Is there someone who would help take care of you if you had to stay in bed for several weeks? | 0 | 1 |  |
| D4. Is there someone you could turn to if you needed to borrow money, get help getting to the doctor, or some other small immediate help? | 0 | 1 |  |
| D5. Is there someone you could turn to if you needed to borrow money for a medical emergency? | 0 | 1 |  |
| D6. Would the people in your personal life give you information, suggestions, or guidance if you needed it? | 0 | 1 |  |
| D7. Is there someone you could turn to if you needed advice to help make a decision? | 0 | 1 |  |
| D8. Is there someone who could take care of your children if you got sick? | 0 | 1 | *-3* |

**CES-D (Center for Epidemiologic Studies – Depression) Scale**

| ***Interviewer reads****:* “Now I would like to ask you some questions about how you have been feeling during the past week. I am going to read you a list of ways you may have been feeling. Please tell me how often in the past week you have felt that way using the following scale.” |
| --- |

*[****Interviewer:*** *Circle the correct answer for each question.]*

|  | **Rarely**  **(<1 day)** | **Some days**  **(1-2 days)** | **Occasionally**  **(3-4 days)** | **Most days**  **(5-7 days)** |
| --- | --- | --- | --- | --- |
| E1. I was bothered by things that usually don’t bother me. | 1 | 2 | 3 | 4 |
| E2. I did not feel like eating; my appetite was poor. | 1 | 2 | 3 | 4 |
| E3. I felt that I could not shake off the blues even with help from my family or friends. | 1 | 2 | 3 | 4 |
| E4. I felt I was just as good as other people. | 1 | 2 | 3 | 4 |
| E5. I had trouble keeping my mind on what I was doing. | 1 | 2 | 3 | 4 |
| E6. I felt depressed. | 1 | 2 | 3 | 4 |
| E7. I felt that everything I did was an effort. | 1 | 2 | 3 | 4 |
| E8. I felt hopeful about the future. | 1 | 2 | 3 | 4 |
| E9. I thought my life had been a failure. | 1 | 2 | 3 | 4 |
| E10. I felt fearful. | 1 | 2 | 3 | 4 |
| E11. My sleep was restless. | 1 | 2 | 3 | 4 |
| E12. I was happy. | 1 | 2 | 3 | 4 |
| E13. I talked less than usual. | 1 | 2 | 3 | 4 |
| E14. I felt lonely. | 1 | 2 | 3 | 4 |
| E15. People were unfriendly. | 1 | 2 | 3 | 4 |
| E16. I enjoyed life. | 1 | 2 | 3 | 4 |
| E17. I had crying spells. | 1 | 2 | 3 | 4 |
| E18. I felt sad. | 1 | 2 | 3 | 4 |
| E19. I felt that people dislike me. | 1 | 2 | 3 | 4 |
| E20. I could not get “going.” | 1 | 2 | 3 | 4 |

**Alcohol Use: WHO Alcohol Use Disorders Identification Test (AUDIT)**

| ***Interviewer reads:*** “Now I am going to ask you some questions about your use of alcoholic beverages during the past 6 months. By a drink we mean 15 milliliters (half an ounce) of absolute alcohol. For example, a 350 ml can or glass of beer, a 150 ml glass of wine, or a drink containing 15 ml of liquor. There are no right or wrong answers to this. Please try to be as honest and as accurate as you can be.” |
| --- |

*[****Interviewer:*** *Read questions as written. Explain what is meant by “alcoholic beverages” by using local examples of beer, wine, vodka, etc. Code answers in terms of “standard drinks”.* ***Circle the correct answer for each question****.]*

|  | **0** | **1** | **2** | **3** | **4** |
| --- | --- | --- | --- | --- | --- |
| F1. How often do you have a drink containing alcohol? | Never  [*Skip to F9*] | Monthly or less | 2 to 4 times a month | 2 to 3 times a week | 4 or more times a week |
| F2. How many drinks containing alcohol do you have on a typical day when you are drinking? | 1 or 2 | 3 or 4 | 5 or 6 | 7, 8, or 9 | 10 or more |
| F3. How often do you have six or more drinks on one occasion? | Never | Less than monthly | Monthly | Weekly | Daily or almost daily |
| F4. How often during the last 6 months have you found that you were not able to stop drinking once you had started? | Never | Less than monthly | Monthly | Weekly | Daily or almost daily |
| F5. How often during the last 6 months have you failed to do what was normally expected of you because of drinking? | Never | Less than monthly | Monthly | Weekly | Daily or almost daily |
| F6. How often during the last 6 months have you needed a first drink in the morning to get yourself going after a heavy drinking session? | Never | Less than monthly | Monthly | Weekly | Daily or almost daily |
| F7. How often during the last 6 months have you had a feeling of guilt or remorse after drinking? | Never | Less than monthly | Monthly | Weekly | Daily or almost daily |
| F8. How often during the last 6 months have you been unable to remember what happened the night before because of your drinking? | Never | Less than monthly | Monthly | Weekly | Daily or almost daily |
| F9. Have you or someone else been injured because of your drinking? | No |  | Yes, but not in the last 6 months |  | Yes, during the last 6 months |
| F10. Has a relative or a friend or a doctor or another health care worker been concerned about your drinking or suggested you cut down? | No |  | Yes, but not in the last 6 months |  | Yes, during the last 6 months |

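### The 15 ml liquor example read to participants contradicts the questionnaire's own definition of a drink, so two AUDIT items (F2 and F3) may over-count spirits

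*Protocol*

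**What the plan says.** Protocol, Appendix H, section on alcohol use (AUDIT). The interviewer reads out a unit, "By a drink we mean 15 milliliters (half an ounce) of absolute alcohol", and then gives three examples. Two are "a 350 ml can or glass of beer, a 150 ml glass of wine". The third is "or a drink containing 15 ml of liquor".

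The interviewer is told to read the questions as written, to explain alcoholic beverages "by using local examples of beer, wine, vodka, etc", and then: "Code answers in terms of" standard drinks.

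Two of the ten items rest on a count of drinks:
- F2: "How many drinks containing alcohol do you have on a typical day when you are drinking"
- F3: "How often do you have six or more drinks on one occasion"

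Alcohol use appears as a behavioral outcome under Objectives, as a predicted decrease under Hypotheses, and in the list under Primary Outcome Variables. The Study Instruments section names AUDIT first for measuring it. Nothing elsewhere in the protocol gives a strength for liquor or corrects the third example.

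**The concern.** One short text contains two incompatible rules for counting spirits. A respondent or interviewer who works from the definition needs 15 ml of pure alcohol for each drink. One who works from the example needs only 15 ml of the beverage. Beer and wine have no such conflict, so the unit behind F2 and F3 can depend on what the person drinks.

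At stake is the classification of spirits drinkers on quantity (F2) and on heavy occasions (F3), within an outcome that the protocol sets out to test. Someone who moved between spirits and beer could also appear to change consumption without doing so.

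The planned checks are unlikely to catch this. The translation review asks whether the intent of the source text is preserved, so a faithful translation carries the conflict into every language. The pilot asks whether items were confusing or hard to answer, and this text sounds clear. Items F1 to F10 do not record beverage type, so the analysis could not undo the conflict from them.

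**Working it through.** **Inputs from Appendix H**
- One drink = 15 ml of absolute alcohol (half an ounce).
- Examples of one drink: 350 ml of beer, 150 ml of wine, 15 ml of liquor.
- F2 scores: 1–2 drinks = 0; 3–4 = 1; 5–6 = 2; 7–9 = 3; 10 or more = 4.
- F3 threshold: six drinks on one occasion.

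**Assumption (not in the documents)**
- Liquor strength 40% by volume, range 35% to 50%.

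**Step 1. The unit itself.** Half an ounce is 14.8 ml (US) or 14.2 ml (imperial), so the 15 ml definition is internally consistent.

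**Step 2. Strength that each example implies** = 15 / volume.
- Beer: 15 / 350 = 4.3%
- Wine: 15 / 150 = 10%
- Liquor: 15 / 15 = 100%

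The first two are plausible strengths and reproduce the definition. The third does so only for pure alcohol. This contradiction needs no outside figure. Liquor here means a beverage, since the interviewer instruction in the same section names vodka as an example.

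**Step 3. Size if spirits are counted by the example.** Alcohol in 15 ml = 15 × strength. Over-count = 15 / (15 × strength) = 1 / strength. Volume that matches the definition = 15 / strength.

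| Assumed strength | Alcohol in 15 ml of liquor | Over-count | Liquor for one defined drink |
| --- | --- | --- | --- |
| 35% | 5.25 ml | 2.86 | 42.9 ml |
| 40% | 6.0 ml | 2.5 | 37.5 ml |
| 45% | 6.75 ml | 2.22 | 33.3 ml |
| 50% | 7.5 ml | 2.0 | 30 ml |

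**Step 4. Effect on F2 at 40%**
- 75 ml of liquor: 75 × 0.40 / 15 = 2 defined drinks (score 0). By the example, 75 / 15 = 5 drinks (score 2).
- 150 ml of liquor: 150 × 0.40 / 15 = 4 defined drinks (score 1). By the example, 150 / 15 = 10 drinks (score 4, the maximum).

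**Step 5. Effect on F3.** Six drinks by the example is 6 × 15 = 90 ml of liquor. At 40% that is 36 ml of alcohol, against the 6 × 15 = 90 ml that the definition requires. 36 / 15 = 2.4 defined drinks (2.1 at 35%; 3.0 at 50%).

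**Step 6. Reach within AUDIT.** F1 and F4 to F10 ask about frequency, consequences and the concern of others, and do not use a drink count. Each of the ten items is scored 0 to 4, so F2 and F3 together carry at most 8 of 40 points.

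**The case against.** The inconsistency itself is hard to dispute. The case on the other side is about its consequences, and most of it stands.

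- **The over-count is conditional.** Respondents hear both the definition and the example, and the coding instruction refers to standard drinks without saying that the liquor example governs. Coding by the definition gives no over-count. A reader might infer that spirits are in fact counted at 2.5 times their alcohol content. The documents support only that they may be, by about that factor, at a strength that has to be assumed.
- **The alcohol score is not inflated 2.5 times.** Only two of ten items are affected. F2 is banded, and a respondent already at ten or more drinks cannot move higher. The protocol does not say that F2 or F3 alone forms the alcohol outcome.
- **Bias between arms is not shown.** All patient participants answer the questionnaire at baseline, 6 and 12 months, so the fault is common to both conditions. The planned model adjusts for the baseline value of the outcome and for country. An artefact from switching beverages is possible, but nothing in the protocol gives the share of spirits or suggests that the intervention shifts it.
- **A correction may come too late.** The Study Timeline puts enrollment and baseline in January–February 2009, yet the References include a conference presentation of July 2009. This text may therefore postdate the start of baseline. Changing the unit between assessments would itself create an apparent change in drinking.

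What does not stand is treating the line as a background typo. Interviewers must read it as written, it supplies the working unit for spirits, and it serves a listed outcome.

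**Conclusion.** The liquor example contradicts the stated unit, and that conclusion rests on the document's text alone. If spirits are counted by the example, F2 and F3 over-count them by about 2.5 times at an assumed 40% strength, or 2.0 to 2.9 times at 50% to 35%. The F3 threshold would then be reached at 90 ml of liquor, or 2.4 defined drinks at 40%.

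The consequence is misclassified drinking level and added noise in two items. The documents do not support reading this as a 2.5-fold inflation of the alcohol outcome or as a biased comparison of arms. The outcome on which the sample size rests, any unprotected sex in the past 3 months, is untouched. This is a minor point, worth correcting because the correction is cheap.

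**What to change.** First establish whether baseline interviews have begun.

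- **If they have not:** change the liquor volume so that it agrees with 15 ml of absolute alcohol, using the strength of the spirits drunk locally. At an assumed 40% this is 37.5 ml, with a range of 30 to 43 ml for 50% to 35%. Make the same change in English and in every translation. The Study Timeline already has a step to pilot and revise questionnaires before enrollment, so the cost is one line per language version.
- **If baseline data exist:** keep the wording the same at every assessment. Report the inconsistency as a limitation of F2 and F3, and add a sensitivity analysis of the alcohol outcome that leaves out those two items. The cost is a sentence in the report and one further model run. The reduced score would have a maximum of 32 instead of 40, so it should not be read against cut-offs for the full scale.

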**Hypotheses**

Project hypotheses focus on the effectiveness of the prevention intervention package on behavioral outcomes, biologic outcomes, and delivery of services in the HIV care and treatment settings. Intervention clinics will integrate the HIV prevention intervention package into routine care of HIV-positive patients; comparison clinics will provide standard of care to HIV-positive patients.

Compared to participants attending comparison HIV clinics, participants at intervention clinics will be more likely over a 12-month period to report or show a(n):

Behavioral

- Decrease in unprotected vaginal and anal sex
- Decrease in number of sex partners
- Increase in number of sex partner(s) getting an HIV test
- Increase in disclosure of HIV status to sex partner(s)
- Decrease in alcohol use
- Increase in adherence to HIV antiretroviral medications

Biologic

- Decrease in unintended pregnancy or partner pregnancy
- Decrease in STIs (i.e., urethral discharge)

Service Delivery

Compared to the comparison clinics, the intervention clinics will:

- Provide more family planning counseling (e.g., safer pregnancy) and services (e.g., contraception) to HIV-positive women and their partners

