Social Support: The Perceived Availability of Support questionnaire asks about participant’s level of social support. Participants report whether they have access to emotional, physical, and financial support needed to deal with challenging situations.

Alcohol use: The World Health Organization’s Alcohol Use Disorders Identification Test (AUDIT) is a 10-item scale assessing problematic drinking (WHO, 2001). Also included are items from the National Institute on Alcohol Abuse and Alcoholism (NIAAA) Task Force on Recommended Alcohol Questions which assesses frequency and amount of alcohol consumed in the past 6 months (NIAAA, 2003).

HIV antiretroviral medications and adherence: Participants will be asked whether they are currently taking HIV medications (including co-trimoxazole prophylaxis), total time taking HIV medications, current medication regimen and adherence to regimen, reasons for missing doses, and reasons for not taking HIV medications (if not taking).

Disclosure: Participants will be asked about disclosure of serostatus to sex partners, family members, relatives, and friends. They will also be asked whether they are worried about people finding out about their HIV status and what might happen if people found out.

Knowledge of HIV/AIDS transmission: Assesses knowledge of methods for sexually transmitting HIV and sources for HIV/AIDS information.

Sexual Risk Behaviors: Assesses behaviors related to possible sexual transmission of HIV. These include relationship status and sexual behaviors with up to 5 partners, concurrent partnerships, condom use, disclosure of serostatus to sexual partner(s), partner(s) HIV testing and serostatus, sex exchange, and physical and sexual violence experiences.

Sexual Self Efficacy: This will include questions about self-efficacy regarding condom use, discussions with partner about topics such as STDs and condom use.

STIs: Participants will be asked whether they have current symptoms of STIs (discharge, genital sores, pain during urination) and have been treated for STIs during the last 6 months.

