- Assess for alcohol use and refer for alcohol counseling (if indicated)
- Assess adherence to ARVs and refer for adherence counseling (if needed)
- Provide condoms
- Refer to lay counselor for in-depth HIV prevention counseling when indicated or desired

Health care providers will communicate these messages over the course of a clinical visit; however, providers may not communicate all messages to a patient during a single visit given time constraints. Providers will be trained to prioritize messages based on patients’ circumstances and they will raise all of these critical issues over the course of their patients’ regular care. In addition, they will encourage patients to follow up with the lay counselors for more in-depth discussions on these topics.

Training: Health care providers, social workers, and pharmacists will attend a 2 day training on integrating prevention into HIV care and treatment settings. Attendees will be trained on the critical role prevention efforts with HIV-positive persons can play in slowing the spread of HIV in their communities, and the importance of integrating prevention for people living with HIV into care and treatment settings. They will be trained to assess prevention issues and deliver prevention messages during regular clinic visits.

Providers and staff will be provided with two different job aids that can be used for delivering the prevention interventions to patients. One job aid is *5 HIV Prevention Steps for PLWHA in HIV Care and Treatment Settings*, which is a one page provider card that summarizes the key behavioral messages and prevention services HIV-positive patients should receive at *every* visit as part of routine care. The second job aid is *HIV Prevention Messages for PLWHA in HIV Care and Treatment Settings,* which is a scripted and illustrated flip chart that clinic staff can use to communicate prevention messages that are tailored to the person’s specific circumstances and partner’s status.

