Group education sessions will last approximately 45 minutes, and will include presentation and discussion of the information and a question and answer session. The lay counselor will use a flip chart designed with illustrations for patients and questions and text on the lay counselor side. The education flip chart also will be used if needed during individual counseling sessions to explain basic information about HIV/AIDS that a patient needs to understand to be able to successfully address a particular counseling issue. These sessions will be conducted in the waiting area of the clinic. Patients attending the clinic that day will be able to participate in these sessions. These sessions are typically conducted by nursing staff in clinics. Having the lay counselors conduct these sessions will allow nurses to perform other duties in the clinic.

Training: Lay counselors will participate in a 4-week training to learn skills in prevention-related counseling and rapid testing and counseling (where permitted) that will make them valuable members of the HIV clinic team. The first two weeks will include training on the importance of prevention and healthy living for persons living with HIV, and the role of the care and treatment clinic for providing prevention information and support. They will be trained to assess patients using standardized screening questions and to help patients address the most important prevention topics for their situation. Counselors will be trained to deliver prevention counseling to patients using the 5As approach described previously. They will be trained to counsel couples in addition to individuals, when indicated or desired. Counselors will also learn how to deliver a brief alcohol intervention for patients who use alcohol regularly. Also, counselors will be trained to conduct group education sessions on the basics of HIV prevention, HIV treatment and adherence, and positive living.

During the next two weeks of training they will be trained to conduct rapid testing on partners and to provide post-test counseling to both (where permitted by country guidelines). The training will include didactic presentations, skills-building exercises, and interactive role-plays to ensure skill acquisition.

Materials:

- Workbook with individual counseling strategies outlined for each prevention topic
- Flip Charts with educational materials for group educational sessions
- Clinic waiting area posters with prevention messages for patients

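### AUDIT item F10 scores up to 4 points for advice that the package itself delivers, so a between-arm comparison of the ten-item total would be biased against the intervention

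*Protocol*

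**What the plan says.** The Hypotheses section lists "Decrease in alcohol use" among the behavioral effects expected in intervention clinics over 12 months. Alcohol use appears again under Primary Outcome Variables in the Variables section. Neither place gives a score, item set or cut-off.

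The Patient Questionnaire section names two alcohol measures. One is the AUDIT, which "is a 10-item scale assessing problematic drinking". The other is a set of NIAAA items, "which assesses frequency and amount of alcohol consumed in the past 6 months". The alcohol section of Appendix H prints only the AUDIT items F1 to F10; no separate NIAAA block appears there.

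F10 asks whether a relative, a friend or "a doctor or another health care worker been concerned about your drinking or suggested you cut down". By the printed columns, a plain no scores 0, an older event scores 2, and "Yes, during the last 6 months" scores 4. A participant who answers never to F1 skips F2–F8 but is still asked F9 and F10.

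The package description gives providers this task: "Assess for alcohol use and refer for alcohol counseling (if indicated"). For lay counselors it says: "Counselors will also learn how to deliver a brief alcohol intervention for patients who use alcohol regularly". Comparison clinics keep their usual services.

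**The concern.** One event has two roles. When an intervention-clinic provider raises a patient's drinking and suggests less of it, the package is being delivered as designed. The protocol records that act as fidelity in Appendix M (item 17) and as patient-reported exposure in Appendix H (Q4k for providers, R6h for counselors). F10 records it again, as a worse alcohol score.

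The error differs by arm, because only one arm is trained to provide the advice. The 6-month follow-up is timed to about six months after the package is integrated into the clinic, so the recall windows at both follow-ups fall essentially within the intervention period, while the baseline window precedes it. Randomization, the clinic random effects and adjustment for the baseline value leave the bias in place, because the extra F10 points arise after baseline and form part of the estimated condition effect. A larger sample would not help either. Better delivery of the alcohol component would increase the bias, so a real benefit on a listed outcome could be reported as small or absent.

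**Working it through.** The protocol states no effect size, standard deviation, drinking prevalence or scoring rule for alcohol, so there is no figure of its own to reproduce. The check is score arithmetic from the printed form.

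**Inputs from Appendix H.** Ten items with column values 0 to 4, so the total runs 0–40. F10 takes 0, 2 or 4. Skipped items are taken as 0 (an assumption).

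**Individual level.** Change in total = change in F1–F9 + change in F10. Hypothetical participants:

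| Participant | F1–F9 before → after | F10 before → after | Total before → after |
|---|---|---|---|
| Moderate drinker who cuts down (F1 2→1, F2 1→0, F3 1→0) | 4 → 1 | 0 → 4 | 4 → 5 |
| Light drinker, recently stopped | 1 → 0 | 0 → 4 | 1 → 4 |
| Heavy drinker, not advised before | 14 → 5 | 0 → 4 | 14 → 9 |
| Heavy drinker, already advised at baseline | 14 → 5 | 4 → 4 | 18 → 9 |

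The first two improve but score worse. The third falls by 5 points instead of 9. The fourth shows no artefact.

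**Arm level, among drinkers.** Let s be the extra share, relative to the comparison arm, whose F10 moves from 0 to 4 because of the package.

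Bias in the mean total = 4 × s.

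- s = 10%: 4 × 0.10 = +0.4
- s = 25%: 4 × 0.25 = +1.0
- s = 50%: 4 × 0.50 = +2.0

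For participants moved from 2 to 4 the factor is 2, giving +0.2, +0.5 and +1.0. Averaged over the whole arm, each figure must be multiplied by the proportion who drink, which is not given.

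**When is a true reduction reversed?** Let d be the true between-arm reduction in F1–F9 among drinkers. The net difference in the total is 4s − d, which is positive only if s > d/4.

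| d | Break-even s | Net at s = 10% | Net at s = 25% | Net at s = 50% |
|---|---|---|---|---|
| 1 point | 25% | −0.6 | 0.0 | +1.0 |
| 2 points | 50% | −1.6 | −1.0 | 0.0 |

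In every cell the total understates the true reduction; only the cell above break-even turns it into apparent harm.

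**Without F10.** The artefact is 0 by construction. The moderate drinker goes from 4 to 1 and the light drinker from 1 to 0.

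**The case against.** The strongest objection is that the protocol nowhere makes the AUDIT total the outcome. It says only that alcohol use should decrease, F1–F3 are already collected, and the choice of score could be left to a SAP, which was not available here. This stands as a condition on the point: the bias arises only if the total, or a cut-off on it, is compared. It does not remove the point. The protocol introduces the instrument as a ten-item scale, the total is the natural way to use such a scale, the second measure it names is not on the printed form, and nothing warns that one item overlaps with the intervention.

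A reader might infer that the score must rise in the intervention arm even as drinking falls. The documents do not support that. The heavy-drinker rows above fall, and the arm mean rises only above the break-even share. Several features also limit that share:

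- Referral is made only where indicated, and the counselors' brief intervention is for regular drinkers, so non-drinkers add little.
- The alcohol section is framed on the past 6 months. Someone abstinent throughout that window would rarely be newly advised, so the example of the participant who stopped fits mainly a recent quitter answering F1 in the present tense.
- Advice received only in the first half of follow-up scores 2, not 4, by 12 months.
- Comparison-clinic staff may give some advice as usual care; only the excess counts.

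A reader might also infer that F10 measures nothing but delivery of the package. That goes too far. It also counts concern from relatives and friends. Lay-counselor sessions may not register at all: counselors are described as having no medical training, and Appendix H itself tells participants that counselors are distinct from health care providers. The provider's advice is the secure link.

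**Conclusion.** The point holds in conditional form. F10 awards up to 4 of 40 points for an act the package trains intervention-clinic providers to perform, so a between-arm comparison of the ten-item AUDIT total, or of a cut-off on it, is biased against the intervention. The direction is known; the size is not. Under an assumed extra share of 10% to 50% of drinkers moved from 0 to 4, the bias is +0.4 to +2.0 points among drinkers, less if some move from 2 to 4, and less again averaged over all participants. It can mask a true reduction; reversal requires a share above one quarter of the F1–F9 drop.

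This should be fixed, but it does not threaten the trial's main result: the sample size and power rest on unprotected sex, not alcohol. The mismatch between the instrument description and Appendix H over the NIAAA items is a separate inconsistency. It matters here because it leaves the AUDIT as the only alcohol measure on the printed form.

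**What to change.** - Define the between-arm alcohol outcome at 6 and 12 months on the consumption items F1–F3, or on the AUDIT total without F10.
- Report the full ten-item total only as a supplement, and do not base the arm comparison on it or on a cut-off applied to it.
- Report F10 by arm beside Q4k and R6h as an exposure measure.
- Reconcile the Patient Questionnaire section with Appendix H: either print the NIAAA items or remove the statement that they are included.

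The outcome definition needs about one sentence and no new data. The small cost is that the standard ten-item total is no longer the comparison score; F1–F3 also leave out drinking consequences, which F1–F9 would keep. The remaining items are still self-reported, a limitation the protocol already acknowledges and this change does not address.
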